# Involved site radiation therapy in stage I-III nasopharyngeal carcinoma with limited lymph node burden (ISRT-NPC) or elective region irradiation: a study protocol for a multicenter non-inferiority randomized controlled phase III clinical trial

**DOI:** 10.1186/s12885-023-11212-7

**Published:** 2023-08-03

**Keywords:** Nasopharyngeal carcinoma, Limited lymph node burden, Involved site radiation therapy, Clinical target volume, Regional control, Toxicity, Quality of life

## Abstract

**Background:**

Current radiotherapy guidelines and consensus statements uniformly recommend elective region irradiation (ERI) as the standard strategy for nasopharyngeal carcinoma (NPC). However, given the scarcity of skip-metastasis, the improved assessment accuracy of nodal involvement, and the striking advancements in chemotherapy for NPC, a one-fits-all delineation scheme for clinical target volumes of the nodal region (CTVn) may not be appropriate anymore, and modifications of the CTVn delineation strategy may be warranted. Involved site irradiation (ISI) covering merely the initially involved nodal site and potential extranodal extension has been confirmed to be as effective as ERI with decreased radiation-related toxicities in some malignancies, but has not yet been investigated in NPC. This study aims to compare the regional control, survival outcomes, radiation-related toxicities, and quality of life (QoL) of ISI with conventional ERI in NPC patients with a limited nodal burden.

**Methods:**

ISRT-NPC is a prospective, multicenter, open-label, noninferiority, phase III randomized controlled trial. A total of 414 patients will be randomly assigned in a 1:1 ratio to receive ISI or ERI. Randomization will be stratified by institution scale and N stage. Generally, in the ISI group, the high-risk CTV1 (dose: 60 Gy) includes a 1-cm expansion of the positive LN as well as the VIIa and the retrostyloid space above the bilateral transverse process of the atlantoaxial spine (C1), regardless of N status. The low-risk CTV2 (dose: 50 Gy) covers the cervical nodal region with a 3-cm caudal expansion below the transverse process of C1 for N0 disease and a 3-cm expansion below the positive LN for positive LNs.

**Discussion:**

The results of this trial are expected to confirm that ISI is a non-inferior strategy to ERI in stage I-III patients with low LN burden, enabling the minimization of treatment-related toxicity and improvement of long-term QoL without compromising regional control.

**Trial registration:**

ClinicalTrails.gov, NCT05145660. Registered December 6, 2021.

## Background

Nasopharyngeal carcinoma (NPC) is one of the most common head and neck malignancies. Southeast Asia is the top epidemic region for NPC, with an age-standardized incidence rate of five (per 100,000 population) [1]. Given the complicated anatomical location and high radiosensitivity of NPCs, radiotherapy is the mainstay of treatment for these tumors. The National Comprehensive Cancer Network (NCCN) guidelines recommend radiotherapy alone for stage I NPC and concurrent chemoradiotherapy (CCRT) with or without induction chemotherapy as the standard treatment for stage II-IVA NPC [2].

Intensity-modulated radiotherapy (IMRT) is well-accepted as the preferred radiotherapy technique in treating NPC. In addition, advancements in chemotherapy, such as the regimen optimization of induction chemotherapy and consolidation metronomic chemotherapy, have been extensively investigated and validated to improve the outcome of NPCs, achieving 5-year overall survival (OS) and local-regional control (LC) rates exceeding 90% for stage II-III NPC [3]. These extraordinary survival rates have yielded a population that will experience not only long-term survival but also marked treatment-related sequelae [4, 5]. Therefore, de-escalation of the therapeutic strategy is required for considerably curable malignancies, with the aim of reducing treatment-related toxicity while maintaining excellent cure rates.

Current guidelines recommend at least 70 Gy of radiotherapy to the gross tumor volume (GTV), namely the primary lesion at the nasopharynx as well as involved lymph nodes (LNs) [2]. The clinical target volumes for the nodal region (CTVn) that have been outlined to cover potential sub-clinically involved areas are generally divided into high- (CTVn1, 60–70 Gy), intermediate- (CTVn2, 60 Gy) and low-risk regions (CTVn3, 50–54 Gy) [6]. The international guidelines uniformly recommend that the CTVn2 includes a higher risk of subclinical lesions in all patients with NPC [6]. Nonetheless, these recommendations are not risk-adjusted for nodal location and burden. The results from our institutional real-world study of 2025 patients revealed that the 5-year regional-recurrence-free survival (RRFS) significantly worsened with an increasing nodal burden (97.6%, 97.5%, 94.6% and 91.8% for N0-3 stages, respectively), which confirmed the significant heterogeneity in stage II-IVa patients [7]. Therefore, subjecting everyone to the same treatment modality may be an arbitrary approach. Furthermore, numerous previous studies have reported that most regional recurrences are observed within the nodal GTV or CTVn1 region with high doses and that the marginal or out-of-field failure rates were below 10% [8, 9]. Therefore, lower-intensity cervical irradiation may be justified for early- to mid-stage patients with a relatively low burden of LNs (LB-LN).

As a part of IMRT, elective region irradiation (ERI), defined as prophylactic irradiation of the entire region of involvement plus at least one subsequent level, has become the standard strategy since the two-dimensional (2D) era [10]. However, ERI inevitably leads to acute and late toxicities closely related to quality of life (QoL), including persistent xerostomia, subcutaneous fibrosis, and mouth-opening difficulties [4, 5, 11, 12]. Furthermore, the radiation-related adverse effects on the lymphatic system reduce lymphocyte counts, impair the preservation of immune function, and even promote tumor growth by limiting the adaptive immune response [13]. Additionally, a combination of radiotherapy and chemotherapy exacerbates treatment-related toxicities, which remains an unaddressed point of concern in the IMRT era [3].

In comparison with ERI, involved site irradiation (ISI), a modified modality performed using cervical irradiation covering merely the initially involved nodal site and possible extranodal extension (ENE), has been confirmed to be quite effective in hematologic malignancies with low radiation-related toxicities [14, 15]. Nevertheless, to the best of our knowledge, no study has reported the validity of ISI in NPC. Given the scarcity of skip node metastases in NPC and the increased sensitivity of diagnostic imaging modalities in detecting occult involved LNs, the introduction of ISI for NPC treatment can be considered to be justifiable [16, 17].

Consequently, this study will apply the ISI strategy in early to mid-stage NPC and compare its regional control rates, survival outcomes, radiation-related toxicities, and QoL with the conventional ERI approach. We hypothesize that ISI with appropriate volume reduction of CTVn can reduce treatment-related toxicities and better preserve immune function without compromising regional control.

## Methods

### Study design

This study is designed as a multicenter, noninferiority, subject-blinded, randomized, phase III trial. A total of 414 patients harboring stage I-III NPC with LB-LN (detailed definition is presented in “Inclusion criteria” section) from eight tertiary hospitals in China will be randomized (1:1) to the ISI or ERI groups. The flow chart and study design schedule are presented in Fig. 1; Table 1, respectively.

**Fig. 1 Fig1:**
[figure not shown]
Flow chart showing the overview of this trial. CTV1, high-risk clinical target volume for the nodal region; CTV2, low-risk clinical target volume for the nodal region; C1, the atlantoaxial spine; ENE, extranodal extension; GTV, Gross tumor volume; Gy, gray; LN, lymph node; MAD, maximum diameter; QoL, quality of life; RPLN, retropharyngeal lymph node

**Table 1 Tab1:** Schedule of study assessment

Period	Pre-RT	During RT			within 2 years after RT	3–5 years after RT	5 years after RT
Time		Weekly	Mid	End	every 3 months	every 6 months	annually
Eligibility	X						
Written informed consent	X						
History	X						
Baseline documentation^$^	X						
Physical examination	X	X	X	X	X	X	X
General laboratory tests^#^	X	X	X	X	X	X	X
EBV-DNA measurement	X	X	X	X	X	X	X
Radiological image examinations							
Nasopharyngoscopy	X		X	X	X	X	X
MRI of nasopharynx and neck	X		X	X	X	X	X
Cervical ultrasound	opt		opt	opt	opt	opt	opt
CT of chest and abdomen	X				every 6 months	X	X
Abdominal CT/ultrasound	X				every 6 months	X	X
ECT bone scan	X				annually	annually	X
PET/CT	opt				opt	opt	opt
Toxicities/Adverse events reporting	If related to study procedures	X	X	X	X	X	X
Quality of life	X		X	X	X	X	X

*RT *Radiation therapy, *EBV *Epstein–Barr virus, *CT *Computed tomography, *ECT *Emission computed tomography, *MRI *Magnetic resonance imaging, *PET *Positron emission tomography.

General laboratory tests include blood routine analysis, biochemistry analysis, urine and stool routine analysis, circular lymphocyte phenotyping, and EBV-DNA measurement. $ includes electrocardiography, pulmonary function measurements, and assessments of hypotension and diabetes.

### Primary endpoint

The 3-year RRFS (Regional-recurrence-free survival, which is measured from the registration to the documented regional recurrence) will be compared between the ISI and ERI groups.

### Secondary endpoint

The effects of ISI on 3-year OS (measured from registration to documented death from any cause or last follow-up), distant metastasis-free survival (DMFS, measured from registration to documented distant metastasis or death from any cause), and progression-free survival (PFS, measured from registration to documented locoregional recurrence or distant metastasis or death from any cause); early (from the start of radiotherapy until the 1 month after radiotherapy) and late toxicities; and general and late toxicity-related QoL will be evaluated.

### Inclusion criteria

Age between 18 and 75 years;Karnofsky performance status (KPS) score ≥ 70;Pathologically confirmed World Health Organization (WHO) type II-III NPC;TNM stage I-III (T1-3N0-2M0) according to the 8th American Joint Committee on Cancer / Union for International Cancer Control (AJCC/UICC) staging system with a maximum diameter (MAD) of cervical involved LNs ≤ 3 cm [18] and without high-grade ENE [19, 20], namely LB-LN;Available baseline nasopharynx and neck computed tomography (CT) or magnetic resonance imaging (MRI) (strongly advocated) data (including functional MRI sequences) and measurable tumor lesions;All procedures for defining the tumor burden completed within 4 weeks of registration;Survival expectancy of at least 6 months;Normal marrow and organ function: hemoglobin ≥ 120 g/L, WBCs ≥ 4 × 10^9^ /L, platelets ≥ 100 × 10^9^ /L; liver and kidney function-related indicators within 1.5*the normal upper limit;Patient willingness to comply with the protocol;Patient willingness and ability to provide an informed consent form.

### Exclusion criteria

MAD of cervical metastatic LNs > 3 cm [18];High-grade ENE of cervical LNs (including matted nodes and LNs infiltrating the adjacent muscle, parotid gland, vessels or skin) [19, 20];AJCC T4 or N3 stage;History of other malignancies (except for stage I non-melanotic skin cancer or in-situ cervical cancer);Pregnant or lactating women or women of childbearing age without contraception;Concurrent enrollment in another interventional clinical trial;Uncontrolled comorbidities that may reduce compliance with the trial, such as myocardial infarction, arrhythmia, cerebrovascular disease, ulcer disease, psychiatric disease, and uncontrollable diabetes;Unwillingness to comply with procedures and requirements as per the study protocol regularly.

### Randomization

An eligibility checklist and patient consent must be completed and obtained before randomization. Eligible patients will be allocated randomly to the ISI and ERI groups on a 1:1 basis using a computer-generated randomization scheme with a block size of four. Randomization will be stratified by institution scale (large vs small) and N stage (N0 vs N1 vs N2).

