### Radiotherapy

Simulation: To ensure consistency in the multicenter setting, the localization and immobilization procedures on CT and MRI will be based on the Chinese Consensus Guidelines for Radiotherapy in NPC (version 2020) [21]. In brief, CT and MRI scans will be performed in the supine position with a thermoplastic mask at the head, neck, and shoulder. The scans will be captured in 3-mm slices from the head to 3 cm below the sternoclavicular joint.

Target volume delineation: The same principles will be shared between the two arms regarding the delineation of GTVnx, GTVnd, and CTV for the primary tumor and organs at risk (OAR). Detailed definition of GTVnd is in accordance with the international guidelines [6]. Suspicious LN is defined as the one with MAD between 5mm and 10 mm as well as ambiguous radiological features. With regard to the CTV for LNs, patients will be randomized to follow the respective strategies of ISI and ERI groups (Table 2). Figure 2 A-C shows the delineation examples of ISI and ERI.

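### A single, published block size of four, with physicians who know each assignment, is an avoidable predictability weakness, mainly where one centre dominates a stratum

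*Protocol article*

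**What the plan says.** The Randomization section fixes the allocation method as one "using a computer-generated randomization scheme with a block size of four", in a 1:1 ratio. On strata it says: "Randomization will be stratified by institution scale (large vs small) and N stage (N0 vs N1 vs N2"). That makes 2 × 3 = 6 strata. Centre is not a factor, although patients come "from eight tertiary hospitals in China will be randomized (1:1) to the ISI or ERI groups" (Study design).

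On blinding, the abstract says "ISRT-NPC is a prospective, multicenter, open-label, noninferiority, phase III randomized controlled trial", while Study design describes a "multicenter, noninferiority, subject-blinded, randomized, phase III trial". Those two labels disagree, which is a separate matter. Under either one the treating physician is unblinded, because the Radiotherapy section says: "With regard to the CTV for LNs, patients will be randomized to follow the respective strategies of ISI and ERI groups (Table 2").

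On sequence, the Randomization section says: "An eligibility checklist and patient consent must be completed and obtained before randomization". Trial status reports that recruitment began in August 2022 and was continuing when the article appeared, so the block size became public while patients were being enrolled.

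**The concern.** With a short block of known, constant length, past assignments reveal future ones. Hiding the list does not prevent this, because the inference uses only assignments already made. Completing the checklist and consent before randomisation does not prevent it either: the decision to approach or defer a patient comes earlier, when N stage is already known.

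Eligibility leaves some room for judgement, since it turns on nodal diameter up to 3 cm and on the absence of high-grade extranodal extension. The Discussion itself links a 3 cm diameter to worse regional control. A physician who expects ISI next and worries about a borderline neck could hold that patient back. Risk in the ISI arm would then be lower, which favours a non-inferiority conclusion, and an intention-to-treat analysis cannot undo selection made before randomisation.

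Few failures are expected. Allowing for 5% dropout, 414 × 0.95 / 2 ≈ 197 patients per arm, and at 96% control about 197 × 0.04 ≈ 8 failures per arm. One failure moves the observed difference by 1/197 ≈ 0.5 percentage points, against a 6-point margin. This only illustrates sensitivity; nothing in the article shows that selection has occurred.

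**Working it through.** The plan gives no predictability figure to reproduce, and the sample size does not depend on this point.

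**Inputs from the article:** block size 4, ratio 1:1 (two ISI and two ERI per block), six strata, eight hospitals. **Assumptions:** one list per stratum; k centres recruiting into a list, with k from 1 to 7 because eight hospitals are split between two scale categories in an unstated way; equal recruitment unless noted; for the simulations, 414 / 6 = 69 patients per list.

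**1. Observer of the whole list who knows where blocks start.** The best guess is the arm with more places left in the block.
- First patient: 1/2 correct.
- Second: 2/3.
- Third: the first two match in 1/3 of blocks, and the third is then certain; otherwise it is an even guess. 1/3 × 1 + 2/3 × 1/2 = 2/3.
- Fourth: always certain.

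Correct guesses: (1/2 + 2/3 + 2/3 + 1) / 4 = 2.833 / 4 = 70.8%.
Known in advance: (1/3 + 1) / 4 = 33.3%.
Over 69 patients (17 full blocks plus one patient): (17 × 2.833 + 0.5) / 69 = 70.5%, the fixed-block figure used in step 4.

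**2. Certainty for a centre that sees only its own patients, even if it knows the block boundaries.** The first three assignments of a block always hold two of one arm. The fourth is certain to its centre only if that centre enrolled both, with probability 1/k². The third is certain with probability 1/(3k²). The share of all assignments known is (1/k² + 1/(3k²)) / 4 = 1/(3k²).

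| Equal centres on the list | Fourth assignment certain | All assignments certain |
|---|---|---|
| 1 | 100% | 33.3% |
| 2 | 25% | 8.3% |
| 3 | 11% | 3.7% |
| 4 | 6% | 2.1% |
| 7 | 2% | 0.7% |

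**3. Average guessing by such a centre (simulated).** It guesses the arm that is behind in its own running count and tosses a coin when level. Correct guesses under fixed blocks of four: 70.5% (k = 1), about 60% for one centre with 90% of the list, 53.9% (k = 2), about 53% (k = 3), about 52% (k = 4) and 51.6% (k = 7).

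**4. Blocks of 4 and 6 in random order (simulated).**
- Full-list observer: correct guesses fall from about 70.5% to about 69%. Assignments known with certainty fall from about 33% to about 5%, because the observer usually cannot tell which block length is running.
- Two or more equal centres: about 54% at k = 2 and about 52% at k = 4, the same as with fixed blocks.
- Largest within-block imbalance: 6 / 2 = 3, instead of 4 / 2 = 2.

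**The case against.** The strongest reply is that the 71% is a worst case. A reader might infer from a fixed block of four that sites can predict the end of every block. The design does not support that. Lists are shared by all hospitals in a scale category, so a local investigator usually sees part of a block and does not know where it began. With two or more equal centres, guessing is little better than chance. The article gives neither the large/small split nor recruitment by centre, so a dominant centre is a possibility and not a documented fact. This part of the objection stands and sets the limits of the point.

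A reader might also infer that the list is not held centrally. The article is silent on allocation concealment, which an article commonly leaves to the full protocol, and no such criticism is made here.

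Two further objections carry some weight. Varied blocks barely change average guessing; that is true, and the gain lies in removing certainty for someone who sees the full list. The scope for selection is also narrowed, because N stage is a stratification factor and larger nodes and high-grade extranodal extension are excluded in both arms. Some room remains within those limits, but its effect on the non-inferiority test has not been quantified.

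**Conclusion.** The point holds as a minor, avoidable weakness. The block size is a stated choice, it was published during recruitment, and treating physicians know the arm under either description of blinding. For an observer of a whole stratum, one third of assignments are known in advance (the fourth in every block, and the third and fourth together in one third of blocks), and about 71% can be guessed. For a typical centre sharing a list the exposure is small: about 60% correct with 90% of the list, and 52–54% with two to four equal centres. The risk therefore matters mainly if one centre makes up or dominates a scale category, or if sites pool assignments. These figures assume one list per stratum and, except for the 90% case, equal recruitment. The documents show neither that selection has happened nor how large any bias would be.

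**What to change.** For patients still to be randomised, generate the remaining list within the same six strata using randomly varied block sizes (for example 4 and 6), and do not disclose the sizes to sites. Whether patients remain is known only as of the article's publication; if recruitment has closed, the change no longer applies.

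The benefit is largest where one centre sees most of a list, and slight where several centres share it evenly. The cost is regenerating the remaining list and accepting a maximum imbalance per stratum of 3 instead of 2. Sample size, endpoint and analysis stay as they are.

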### Pre-treatment evaluation (baseline)

The enrolled patients are required to complete the following examinations within 4 weeks before registration:

Thorough medical history and physical examination: evaluation of KPS score, weight, height, vital signs, and physical examination of the nasopharynx, cervical LNs, and nervous system.Laboratory tests: blood routine examinations, biochemistry evaluations, urine and stool routine analysis, circular lymphocyte phenotyping, and measurement of Epstein–Barr virus (EBV) DNA concentration.Radiological imaging examinations: fiberoptic nasopharyngoscopy and tumor biopsy, MRI and CT contrast imaging of the nasopharynx and neck, cervical ultrasound, chest CT, abdominal CT/ultrasound, emission computed tomography (ECT) bone scans, and positron emission tomography (PET)/CT (optimal; performed at the discretion of the attending physician).Baseline documentation: electrocardiogram, pulmonary function, and QoL assessment.

### Radiotherapy

Simulation: To ensure consistency in the multicenter setting, the localization and immobilization procedures on CT and MRI will be based on the Chinese Consensus Guidelines for Radiotherapy in NPC (version 2020) [21]. In brief, CT and MRI scans will be performed in the supine position with a thermoplastic mask at the head, neck, and shoulder. The scans will be captured in 3-mm slices from the head to 3 cm below the sternoclavicular joint.

Target volume delineation: The same principles will be shared between the two arms regarding the delineation of GTVnx, GTVnd, and CTV for the primary tumor and organs at risk (OAR). Detailed definition of GTVnd is in accordance with the international guidelines [6]. Suspicious LN is defined as the one with MAD between 5mm and 10 mm as well as ambiguous radiological features. With regard to the CTV for LNs, patients will be randomized to follow the respective strategies of ISI and ERI groups (Table 2). Figure 2 A-C shows the delineation examples of ISI and ERI.

**Fig. 2 Fig2:**
[figure not shown]
**A** Comparison of CTV delineation between the ISI and ERI groups in patients with N0 disease (Upper panel: ERI; Lower panel: ISI). CTV, clinical target volume; ERI, elective region irradiation; ISI, involved site irradiation. **B** Comparison of CTV delineation between the ISI and ERI groups in patients with ipsilateral positive LNs in level II extending to level III (Upper panel: ERI; Lower panel: ISI). CTV, clinical target volume; ERI, elective region irradiation; ISI, involved site irradiation; LN, lymph node. **C** Comparison of CTV delineation between the ISI and ERI groups in patients with bilateral positive LNs (Upper panel: ERI; Lower panel: ISI). CTV, clinical target volume; ERI, elective region irradiation; ISI, involved site irradiation; LN, lymph node

**Table 2 Tab2:** Delineation of the ISI and ERI groups

	ISI	ERI
GTVnx	Apparent macroscopic primary lesion at the nasopharynx based on detailed physical examination, fiberoptic nasopharyngoscopy, and diagnostic CT, MRI or PET/CT images	
GTVrpn	Positive RPLN	
GTVnd	Positive cervical LN	
High-risk CTV1	GTVnx plus a 10-mm margin to encompass the microscopic extension of the gross tumor, the whole nasopharynx, the high-risk structures recommended for CTVp2 by the contouring consensus* (such as parapharyngeal space, skull base, pterygopalatine fossa and the inferior part of the nasal cavity and maxillary sinus), the VIIa, and the retrostyloid space above the bilateral transverse process of C1.	
N0	Suspicious LN (if available)	Bilateral level II
N1-2	Geometrically 1-cm expansion of the positive LN (GTVnd) or GTVrpn, without exceeding anatomical barriers; Suspicious LN (if available)	The whole involved level + at least one subsequent level
Low-risk CTV2		
N0	Bilateral cervical nodal region with the 3-cm caudal expansion below transverse process of C1 and at least covering the level II; 1-cm expansion of the suspicious LN (if available)	Bilateral level III + Va
N1-2	Ipilateral cervical nodal region with the 3-cm expansion below the positive LN (GTVnd) and at least covering the level II; contralateral cervical nodal region with the 3-cm caudal expansion below the transverse process of C1 and at least covering the level II; 1-cm expansion of the suspicious LN (if available)	At least one subsequent level below CTV1
*PGTVnx, PGTVrpn, PGTVnd, PGTVns, PTV1, PTV2 are generated by geometric 3-5mm expansion of the GTVnx, GTVrpn, GTVnd, GTVns, CTV1 and CTV2, respectively. Abbreviations: CTV *Clinical target volume, * GTV *Gross tumor volume, *LN *Lymph node, *ISI *Involved site irradiation, *ERI *Elective region irradiation, *nx *nasopharynx, *rpn/RPLN *retropharyngeal lymph node, *ns* suspicious LN		

3.Dose prescription and suggested dose constraints of OARs: As per the latest ASCO/CSCO and NCCN guidelines, dose prescription is shown in Table 3. Dose constraints of OARs are based on those recommended in the 2020 international guideline on dose prioritization for NPC [22].

**Table 3 Tab3:** Dose prescription

Target volume	Total dose (Gy)	Fraction dose (Gy)	Fractions
PGTVnx	69.96	2.12	33
PGTVrpn	69.96	2.12	33
PGTVnd	69.96	2.12	33
PGTVns	60.06	1.82	33
PTV1	60.06	1.82	33
PTV2	50.96	1.82	28
*PGTV *Planning gross tumor volume, *GTV *Gross tumor volume, *PTV *Planning target volume, *nx* nasopharynx, *rpn *retropharyngeal lymph node			

